# For girls and women (4GW) HPV RCT protocol: a crowdsourced, pragmatic stepped-wedge cluster randomized trial to improve uptake of HPV vaccination and screening among mother-daughter dyads in Nigeria

**DOI:** 10.1186/s13012-025-01428-5

**Published:** 2025-05-01

## Abstract

**Background:**

Expanding human papillomavirus (HPV) vaccination for girls and HPV self-collection for women can reduce the global burden of cervical cancer. However, HPV vaccination and self-collection services are rarely implemented simultaneously in mother-daughter dyads, leaving a critical gap in cervical cancer prevention. From 2023 to 2024, a community-engaged model for combined HPV vaccination and screening was co-designed using crowdsourcing open calls and designathons with mother-daughter teams and pilot-tested by trained research facilitators. This study explores the impact of this crowdsourced, community-engaged mother-daughter campaign and implementation strategy bundle on HPV vaccination among girls and HPV screening among their mothers in Nigeria over 6 months in 18 Nigerian local government areas (LGAs).

**Methods:**

A hybrid effectiveness-implementation type II pragmatic stepped-wedge cluster randomized control trial has been employed to the effectiveness of an implementation strategy bundle; a crowdsourced, tailored, community-engaged, mother-daughter HPV campaign on increasing uptake of HPV vaccination among girls aged 9–14 and HPV screening uptake among women aged 30–49 in Nigeria. The mother-daughter campaign will be tailored to local sites and conducted among 612 mother-daughter dyads (1,224 participants) recruited from 18 LGAs in six geopolitical zones of Nigeria. Trained community health workers will collect baseline data and implement a mother-daughter campaign that will provide education on cervical cancer control and access to onsite services for HPV vaccination and screening in a private area while engaging mothers and daughters simultaneously to increase uptake of the services. A mixed-methods evaluative and iterative assessment will be conducted using Proctor’s Implementation Outcomes Framework and the PEN- 3 cultural model. The primary outcomes are the uptake of HPV preventive measures—HPV vaccination (one dose) among girls (ascertained by onsite clinical records of vaccine uptake) and HPV self-collection completion among mothers (ascertained by laboratory receipt of self-collected specimens) within six months of trial enrollment. Pre-post effectiveness and cost of study components are embedded in the implementation and sustainment phases, compared to pre-implementation data assessed for each LGA.

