### Study setting aims and approach

#### Setting

Nigeria’s population is estimated at over 200 million, of which 49.3% are female [50, 51]. The country has 36 states mapped into six geopolitical zones with a Federal Capital territory [50]. There are also 374 distinct ethnic groups and indigenous languages spoken throughout its 36 states and Federal Capital Territory [50]. Data from the most recent Demographic Health Survey (2018) estimates that the median age at first sexual intercourse among women is 17 years of age and first marriage at 19 years [52]. Nearly half of women aged 25–49 give birth for the first time before age 21, while 19% of teenage women aged 15–19 have begun childbearing [52]. The Literacy rate in Nigeria is 60% [53]. Also, 65% of women aged 15–49 are employed or self-employed [52], while the monthly minimum wage is 30,000 naira ($18.4) [54]. Although HPV vaccine coverage has increased with the nationwide rollout at 75% [55], it remains notably below the 90% target needed to eliminate cervical cancer as a public health concern. Additionally, despite recommendations for routine cervical cancer screening for women aged 30–49, cervical cancer screening coverage remains under 10% [56, 57]. HPV self-sampling, a potentially accessible method for increasing screening uptake, is also not yet widely implemented or routinely practiced in Nigeria. Organized cervical cancer screening programs are limited, particularly in community settings where most individuals receive healthcare. Our partnership with the Nigerian Institute for Medical Research is critical for enhancing the feasibility of the study. As the key research hub within the Nigerian Ministry of Health, NIMR is well-positioned to design and deliver the intervention across the 18 recruited local government areas within the six geopolitical zones of Nigeria (See Fig. 1).

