#### Outcomes

Among daughters, the primary outcome will be HPV vaccination receipt (one dose) within 6 months of trial enrollment. Vaccines will be provided onsite at the Mother-Daughter Day campaign by study nurses following similar procedures for HPV vaccination during the national rollout [61]. Among mothers, the primary outcome will be self-collection completion within 6 months of trial enrollment, which will also be operationally defined by the receipt of specimens at the NIMR laboratory. As a secondary outcome, we explore HPV vaccine confidence, hesitancy and screening confidence, and the linkage to follow-up care and treatment of women with positive HPV results will be tracked. Using the validated Weiner's surveys, we will assess the acceptability and appropriateness of intervention components from both the daughters'and mothers'perspectives [62]. These surveys include 4 items, each scored on a 5-point scale [62]. Penetration will be explored using the Levels of Institutionalization Scale [63] to assess the extent to which components of the mother-daughter HPV campaigns are institutionalized within participating local government areas. We will also assess plans for sustaining [59] intervention components that will include 3-item leadership support for implementing the HPV campaign, a 3-item scale on responsiveness to mother-daughter preferences and needs for HPV preventive campaigns, an 8-item scale on coalitions, and partnerships to sustain the project, the 9-item infrastructure and capacity to support sustainability and the 3-item monitoring and evaluation tool from the sustainment measure on a 5-point scale [64]. We will also assess the intervention fidelity [65] and track adaptations made using the FRAME-IS [66] tool for reporting adaptation across the 18 LGAs.

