### Statistical analysis

#### Data analysis

The primary analyses will examine rates of HPV self-collection (mothers) and single-dose vaccine receipt (daughters). Analyses will be performed separately for the mother sample and daughter samples. The main analyses will compare the rates of HPV self-collection (mothers) and vaccine uptake during the pre-and post-intervention periods. We will examine a hypothesis comparing the superiority of the intervention with pre-intervention periods using the stepped-wedge cluster randomized control design and account for any temporal changes in HPV vaccination or screening rates during the 6-month conduct of the trial. This analysis will be accomplished with generalized linear mixed models to account for the within-person factor – time (baseline, 3 months, and 6 months) and one primary between-person factor (randomization site dummy code as 0 = convention and 1 = intervention). The 3-level model is structured as observations nested within subjects within local government areas. Multilevel modeling software (SAS, version 9.4, PROC GLIMMIX with logit as link function) will be used to compute full information maximum likelihood (FIML) estimates of the model parameters. The model will include intervention status and time as fixed effects and site and individuals as random effects. The estimated intervention effects will be reported with 95% CIs and p values. Secondary analyses will explore linkage rates to clinical follow-up after positive HPV testing in pre-intervention and post-intervention periods.

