## Discussion

The development of rigorous crowdsourced implementation science strategies is a critical need for the field of implementation science globally. This pragmatic hybrid effectiveness-implementation type II stepped-wedge cluster randomized control trial is a collaborative effort between researchers from the Washington University School of Medicine, University of North Carolina Chapel Hill, Monash University (Australia), Wake Forest University School of Medicine and the Nigerian Institute of Medical Research (NIMR) that responds to this need and is intended to strengthen the use of crowdsourced strategies to improve uptake of HPV vaccination and HPV screening in Africa. While explanatory trials seek to understand the benefit of an intervention under controlled conditions using carefully selected participants [72], pragmatic trials have fewer eligibility requirements and broader potential generalizability. We will test the hypothesis that a combined mother-daughter campaign implemented by CHWs and tailored and adapted to local contexts, with education on cervical cancer and onsite services provided (i.e. access to HPV vaccination and HPV screening in private spaces), increases HPV vaccination among girls and HPV self-collection among mothers in Nigeria recruited from 18 local government areas. The primary outcomes will be HPV preventive measures: HPV vaccination uptake (one dose) among girls, verified through clinic records, and the return of HPV self-collection kits among mothers, confirmed by laboratory receipt of self-collected specimens. The secondary outcomes are HPV vaccine confidence, vaccine hesitancy, linkage and receipt of follow-up care among women with positive (abnormal) HPV self-collection results and implementation outcomes guided by Proctors Implementation Outcomes Framework [41]. HPV vaccinations and HPV screening are evidence-based interventions to reduce the burden of cervical cancer. While the nationwide rollout of HPV vaccinations for girls has begun in Nigeria [61], there remains limited data on the nationwide rollout of HPV screening for women. Furthermore, in Nigerian culture, mothers primarily influence their daughter’s health behaviors, creating and supporting opportunities that influence their health. Despite the key roles that they play, most HPV prevention interventions in Nigeria have minimally involved both mothers and daughters in intervention design and implementation, despite the evidence to support its feasibility and acceptability.

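### The daughters' primary outcome is tied to the campaign's own onsite records, so rollout doses in control periods may go uncounted, and the planned 10–20% baseline does not fit how either outcome is measured

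*Protocol article*

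**What the plan says.** **Daughters.** The abstract's Methods paragraph gives the outcome and its source: "HPV vaccination (one dose) among girls (ascertained by onsite clinical records of vaccine uptake". The Outcomes section defines it as receipt of one dose within 6 months of enrollment and then says "Vaccines will be provided onsite at the Mother-Daughter Day campaign by study nurses". The Discussion describes the same outcome as "HPV vaccination uptake (one dose) among girls, verified through clinic records", without the word onsite.

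**Mothers.** The abstract gives "HPV self-collection completion among mothers (ascertained by laboratory receipt of self-collected specimens) within six months of trial enrollment", and Outcomes says the same: "which will also be operationally defined by the receipt of specimens at the NIMR laboratory". Under Recruitment, kits are offered as an onsite service at the event. The Setting section says of self-sampling that it "is also not yet widely implemented or routinely practiced in Nigeria".

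**Comparator, schedule and planning rates.** The comparator is usual care (Methods). The Introduction and Setting describe a national single-dose vaccine rollout, with stated coverage of 75%. Outcomes are measured every three months in all clusters (Randomization section). The power section and Table 3 use baseline rates of 0.10, 0.15 and 0.20 for both outcomes.

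**Linkage.** The secondary analyses will "explore linkage rates to clinical follow-up after positive HPV testing in pre-intervention and post-intervention periods".

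**The concern.** In a stepped-wedge trial the effect is the difference between what is recorded in control and in intervention periods. It is fair only if an event has the same chance of being recorded in both. Onsite event records exist only once the campaign has reached a cluster, but free vaccination is available outside the campaign throughout. Under the abstract's wording, a girl vaccinated through the rollout in a control period scores 0, and the same girl vaccinated at the event scores 1. A shift in where girls are vaccinated would be read as a rise in uptake.

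The mothers' outcome raises a different problem. If self-collection hardly exists outside the campaign, a control rate near zero may be the truth. It does not fit the 10–20% used to plan the trial, and very few control events could make the planned logit model unstable.

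**Working it through.** **1. What each section implies for a girl vaccinated through the rollout in a control period**

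| Section | Wording in brief | Is that dose counted? |
|---|---|---|
| Abstract, Methods | onsite clinical records | No, if literal |
| Outcomes | receipt of one dose; vaccines given at the event | Source not stated |
| Table 4, adoption | proportion of eligible girls with receipt, at baseline, 3 and 6 months | Source not stated |
| Power section, Table 3 | 10–20% at baseline | Implies yes |
| Discussion | clinic records | Yes, if other clinics qualify |

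These cannot all hold. No section names a source for doses given outside the event that applies in both conditions.

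**2. Reproducing Table 3**

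Inputs from the power section: I = 18 clusters, 34 dyads per cluster, four intervention periods, two-sided alpha 0.05, 80% power. My choices: T = 5 periods, waves of 5, 4, 4 and 5 clusters (the best fit of those tried), m = 34/5 = 6.8 per cluster-period, σ² = mean of p(1−p) over the two conditions, τ² = σ²·ICC/(1−ICC), s² = σ²/m.

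Hussey–Hughes variance: Var = I·s²(s² + Tτ²) / [(IU − W)s² + (U² + ITU − TW − IV)τ²].

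- U = 5·4 + 4·3 + 4·2 + 5·1 = 45
- W = 0² + 5² + 9² + 13² + 18² = 599
- V = 5·16 + 4·9 + 4·4 + 5·1 = 137
- IU − W = 810 − 599 = 211
- U² + ITU − TW − IV = 2025 + 4050 − 2995 − 2466 = 614

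Example, baseline 0.10, follow-up 0.22, ICC 0.01: σ² = (0.0900 + 0.1716)/2 = 0.1308, s² = 0.01924, τ² = 0.00132, standard error 0.0429. Then 0.12/0.0429 = 2.80, which gives 80% power.

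| Baseline | Table 3 (ICC 0.005, 0.01, 0.05) | Recomputed |
|---|---|---|
| 0.10 | 0.216, 0.220, 0.235 | 0.217, 0.220, 0.235 |
| 0.15 | 0.283, 0.285, 0.300 | 0.281, 0.285, 0.301 |
| 0.20 | 0.342, 0.346, 0.362 | 0.342, 0.346, 0.362 |

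All agree within 0.002. The power arithmetic is sound; the question is whether the stated outcome can record the baseline rates put into it.

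**3. The literal reading as a limiting case**

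Assume true uptake c in both conditions (no effect), fully recorded under intervention and not at all under control. The recorded difference is c − 0 = c. The chance of a significant result uses the same formula with a control rate of 0.

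| c | Spurious effect | P(significant), ICC 0.005 / 0.01 / 0.05 |
|---|---|---|
| 0.10 | 10 points | 98% / 98% / 95% |
| 0.15 | 15 points | above 99% throughout |
| 0.20 | 20 points | about 100% throughout |

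If the campaign does work and reaches the expected 65%, the recorded difference would be 0.65 against a true 0.65 − c = 0.55, 0.50 or 0.45. That is an inflation of 0.10/0.55 = 18%, 0.15/0.50 = 30% or 0.20/0.45 = 44%.

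**4. Mothers: model behaviour with few control events**

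With a recorded control rate of 0, the minimum detectable rate becomes 0.050, 0.052 and 0.063, so Table 3 no longer describes the comparison. Simulated logit fits with period effects (no random effects, intervention rate 50%, three runs at each control rate) gave:

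- control 0%: coefficient about 25.6, standard error above 15,000 (no finite estimate)
- control 10%: coefficients 1.8 to 2.6, standard errors 0.28 to 0.32
- control 20%: coefficients 1.0 to 1.6, standard errors 0.24 to 0.25

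**5. Linkage**

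A pre-intervention linkage rate needs women who tested HPV-positive before the campaign. Table 1 excludes mothers screened in the last 5 years, and the kits come with the event, so few such women can be expected.

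**The case against.** A reader might infer that control uptake is zero by construction for both outcomes, so that both effects are inflated or cannot be estimated. The document does not support that.

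- **No section states a zero.** Outcomes and Table 4 define the daughters' outcome as receipt, measurement is scheduled in all clusters, the abstract mentions pre-implementation data for each LGA, and the power section expects 10–20%. These point to a non-zero measured control rate. This stands: the fault is contradictory text, one version of which would bias the result.
- **Mothers.** The hypothesis concerns self-collection, and laboratory receipt measures it objectively. If self-collection is not routine, a low control count is largely correct and the contrast is not inflated by measurement. This stands. Replacing the outcome with any cervical screening would change the hypothesis and is not needed.
- **Estimability.** Divergence needs no control events at all; with 10–20% recorded, the fits behave normally. This stands, and handling of sparse events may be in an analysis plan not shown.
- **Linkage as 0/0.** The 5-year exclusion applies at enrollment and does not prevent later screening, so a strictly empty denominator does not follow.
- **Size.** The 75% national coverage is not the background rate here, because recently vaccinated girls are excluded. Assuming that every control dose is missed is a worst case.
- **A condensed article may omit record sources.** That would excuse silence. Here a source is stated, it depends on exposure, and another section states it differently, so the objection does not remove the point.

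**Conclusion.** The point holds for the daughters' primary outcome. As worded in the abstract, ascertainment depends on exposure, and it conflicts with the Discussion and with the planned baseline. If the literal wording governs and true uptake is 10–20% in both conditions, with complete recording under intervention and none under control, a campaign with no effect would show 10–20 percentage points and would reach significance with a probability of about 95% or more. This range borrows the protocol's own planning rates and is an illustration, not a forecast. Partial capture of control-period doses would shrink the bias in proportion.

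For mothers the finding is narrower: a likely near-zero control rate disagrees with the 10–20% in Table 3 and could destabilise the logit estimate. The linkage comparison will probably rest on very few pre-intervention positives; it is secondary and exploratory.

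**What to change.** 1. **Daughters.** Define the primary outcome as a first HPV dose from any source (vaccination card, facility or immunisation register, or onsite record) with its date. Ascertain it in the same way in control and intervention periods, at the contacts already scheduled.
2. **Consistency.** Make the abstract, Outcomes, the power section and the Discussion agree on that definition and on the control rate it implies.
3. **Mothers.** Keep self-collection with laboratory receipt. Reconcile the 10–20% baseline in Table 3 with the Setting section's account of current practice, and restate the detectable rate if the expected control rate is near zero.
4. **Linkage.** Report it mainly among women who test positive in the campaign, and show any pre-intervention cases descriptively.

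The cost is revised wording, a question or two with a card or register check at existing contacts, and a rerun of the power table for mothers. The vaccination effect may look smaller, and some outside doses will rest on cards or report. The change is best made before control periods end, since doses not captured at the time may be hard to recover.

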### Participants

Our stepped-wedge cluster-randomized trial will consist of two types of participants: 1) mother-daughter dyads recruited from 18 randomly selected LGAs across six geo-political zones in Nigeria with access to NIMR-affiliated clinical staff and 2) CHWs (one per LGA) and supervisors (one per LGA) implementing the intervention. Study eligibility criteria are described in Table 1.

**Table 1 Tab1:** Inclusion and exclusion criteria

Inclusion criteria (mother-daughter dyads)	• Both the mothers'/caregivers’ (between ages 30–49 years) and daughters'(Between 9 to 14 years) willingness to participate in the study• All participants must agree to informed consent in English or Pidgin English, Nigeria's second most common language.• Parental or guardian’s cell phone number for follow-up
Exclusion criteria (mother-daughter dyads)	• Inability to comply with the study protocol • Girls with recent vaccination for HPV or mothers recently screened for cervical cancer (within the last 5 years) • Illness, cognitive impairment, or threatening behaviour with acute risk to self or others

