#### Randomization and rationale for stepped-wedge design

The 18 LGAs will be randomly allocated to the intervention, 4–5 LGAs per month for 12 months. All sites begin as part of the control condition and are block-randomized into four waves, with each wave beginning two months after the start of the prior wave and lasting for 6 months, followed by a 6-month follow-up period. All clusters will eventually receive the intervention, with outcomes measured every three months across all clusters. See Fig. 2for a schematic of the stepped-wedge cluster RCT design. Randomization will be conducted by the study statistician, who will not have direct contact with the LGAs. All LGAs will be informed of their assigned intervention wave before the first wave begins. Blinding was not implemented in this study, as all sites will eventually receive intervention, reflecting typical conditions in real-world settings. The stepped-wedge design was deemed acceptable and ethical by key program partners (NIMR and the Nigerian Ministry of Health) and study collaborators for logistical and pragmatic reasons, given the potential benefits of the intervention package (i.e., combined cervical cancer prevention strategies of vaccination and screening) and the equitable provision of the intervention to all sites [40].

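### Sustainment-phase effectiveness is set against each LGA's own earlier data when no LGA is left in control, so it should be reported as descriptive

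*Protocol article*

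**What the plan says.** - **Comparator.** The Abstract (Methods) states: "Pre-post effectiveness and cost of study components are embedded in the implementation and sustainment phases, compared to pre-implementation data assessed for each LGA". This names effectiveness, a phase (sustainment) and a comparator (the same LGA earlier).
- **Schedule.** Under Randomization and rationale for stepped-wedge design, the 18 LGAs are "block-randomized into four waves, with each wave beginning two months after the start of the prior wave and lasting for 6 months", and six months of follow-up come after that. All clusters cross over, and outcomes are measured every three months.
- **Outcomes.** "Among daughters, the primary outcome will be HPV vaccination receipt (one dose) within 6 months of trial enrollment". "Among mothers, the primary outcome will be self-collection completion within 6 months of trial enrollment". The Methods section follows all dyads for 12 months.
- **Eligibility.** Table 1 excludes "Girls with recent vaccination for HPV or mothers recently screened for cervical cancer (within the last 5 years".
- **Model.** The Data analysis section specifies a generalized linear mixed model with intervention and time as fixed effects and time levels of baseline, 3 and 6 months. Its purpose includes to "account for any temporal changes in HPV vaccination or screening rates during the 6-month conduct of the trial".
- **Timing of uptake.** Table 4 lists uptake at baseline, 3 and 6 months. Its 12-month entries are socio-demographics and the sustainment subscales.

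**The concern.** A stepped-wedge trial separates the campaign from the calendar by comparing LGAs that have crossed over with LGAs that have not. A before-after comparison within each LGA drops that protection. Its null hypothesis is that nothing has changed since before the campaign, not that the campaign has no effect.

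Two features of this trial make that matter. First, girls can be vaccinated through a national rollout that is under way, with coverage put at 75% in the Setting section. Second, a girl who has had her dose stays vaccinated, so a cumulative count carries delivery-phase doses into follow-up and cannot reveal that new uptake has stopped.

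A before-after gain labelled as sustained effectiveness, printed beside the randomised result and tied to cost in the same sentence, could be read as evidence that the effect lasts. The article says its results are meant to inform decision-makers, including on cost-effectiveness.

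**Working it through.** **Is the plan's own calculation in question?** No. The article gives no figure for the sustainment comparison. Its power figures (Table 3) can be reproduced with the Hussey–Hughes variance: 4 steps, 5 periods, 34/5 = 6.8 dyads per cluster-period, and assumed wave sizes of 5/4/4/5. Power at the nine stated rates comes to 0.788–0.809, against the stated 0.80.

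**Step 1: the calendar.** Wave w starts at month 2(w − 1), delivers for 6 months, and is then followed for 6 months.

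| Wave | Leaves control | Follow-up opens | Follow-up closes |
|---|---|---|---|
| 1 | 0 | 6 | 12 |
| 2 | 2 | 8 | 14 |
| 3 | 4 | 10 | 16 |
| 4 | 6 | 12 | 18 |

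The last LGAs leave control at 3 × 2 = 6 months, and the first follow-up opens at 0 + 6 = 6 months. Of 18 × 6 = 108 follow-up LGA-months, none coincides with a control month anywhere. An initial all-control period moves both dates equally and changes nothing. The same section also speaks of 4–5 LGAs per month; if waves started monthly, the last crossover would be earlier still (month 3).

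**Step 2: reach of the time adjustment.** The model's time levels end at 6 months, so as written it does not cover the sustainment phase.

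**Step 3: direction of the change.** For a once-only event in the same dyads, cumulative uptake after minus before equals new uptake divided by dyads, which is at least 0. With no campaign effect it equals background uptake b. If b were 10–20%, the range Table 3 uses for baseline rates, a campaign with no effect would show +10 to +20 points when uptake at entry is zero.

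**Step 4: illustration under no campaign effect.** From the article: 18 LGAs × 34 dyads = 612, ICC 0.005–0.05, two-sided 0.05. Assumed: b, a cumulative outcome, and a t-test on the 18 LGA changes with beta-binomial clustering. Chance of a significant increase, with zero uptake at entry:

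| b | ICC 0.005 | ICC 0.01 | ICC 0.05 |
|---|---|---|---|
| 1% | 63% | 56% | 20% |
| 2% | 97% | 95% | 66% |
| 5% | ~100% | ~100% | 99% |

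If uptake at entry is instead allowed to range over 0–20%, the figures become 14–65% at b = 1%, 55–97% at 2% and 99–100% at 5%.

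An exact McNemar test that ignores clustering needs at least 6 new events out of 612 (2 × 0.5⁶ = 0.031, whereas 5 events give 0.0625). It rejects in 0% of trials at b = 0, 9% at 0.5%, 57% at 1% and 98% at 2%.

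**The case against.** The strongest reply is that this rests on one abstract sentence.

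- **No sustainment-phase uptake outcome is defined.** The primary window is 6 months, and what Table 4 carries to 12 months is mainly scales on leadership, partnership, infrastructure and monitoring. This stands: a cumulative 12-month outcome is an inference, so the argument is conditional on it.
- **Pre-post may be shorthand for the stepped-wedge model.** The Data analysis section also speaks of pre- and post-intervention periods before specifying that model. This is possible for the implementation phase. It cannot rescue the sustainment phase, where there is no concurrent control and the model's time levels have ended.
- **Loss of controls after the last step is inherent to the design.** True, and it is not itself an error. The error is naming an effectiveness comparison for that phase.
- **Background uptake may be zero or not counted.** For mothers this carries weight: the Setting section says self-sampling is not routine, and completion requires receipt at the study laboratory. For daughters it carries less. The Abstract counts vaccination from onsite records, so outside doses may be missed, but then the starting value is about zero by construction and a dose merely moved from the national programme to the campaign counts as a gain.

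A reader might infer that the comparison shows an increase whatever the campaign did. The documents do not support that. It needs background uptake that is above zero and counted, or displaced doses. The 75% figure is national coverage, not the rate of new uptake among enrolled girls.

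**Conclusion.** The point holds as a fault in a stated supporting comparison. On the two-month wave schedule, 0 of 108 follow-up LGA-months have a concurrent control, and the planned time adjustment does not reach them. A before-after change in that phase therefore cannot be attributed to the bundle. If the outcome is cumulative, it also cannot show that uptake failed to be sustained.

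The size of the bias is not known from the article. The 55–97% at 2% background and 99% or more at 5% are illustrations that rest on assumed background rates, an assumed LGA-level test and a cumulative outcome; at 0% there is no false increase. The risk is plausible for daughters and much weaker for mothers.

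Nor should this be read as undermining the main result. The primary effect comes from the randomised stepped-wedge model, which has LGAs in control before month 6, and it is not affected by this point.

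**What to change.** 1. In the Abstract and the Data analysis section, state that effectiveness is concluded only from the randomised stepped-wedge comparison, in periods when some LGAs are still in control.
2. Remove pre-post effectiveness for the sustainment phase, or label it descriptive. Make no effect claim against pre-implementation data, and say that there is no concurrent untreated comparator.
3. Settle whether uptake is collected after 6 months. The three-monthly measurement in the randomization section suggests that it is; Table 4 does not list it. If it is, report new vaccinations and new completed self-collections among those not yet vaccinated or screened, with 95% CIs.

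Items 1 and 2 cost only wording. Item 3 costs one descriptive table if the data are already being collected; otherwise uptake would have to be added to the later visits. The downside is that the trial gives up a claim of sustained effectiveness against pre-implementation, which the design cannot support.
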